## Abstract

**Background:**

Acute lower respiratory tract infection (LRTI) is one of the most common conditions managed internationally and is costly to health services and patients. Despite good evidence that antibiotics are not effective for improving the symptoms of uncomplicated LRTI, they are widely prescribed, contributing to antimicrobial resistance. Many of the symptoms observed in LRTI are mediated by inflammatory processes also observed in exacerbations of asthma, for which there is strong evidence of corticosteroid effectiveness. The primary aim of the OSAC (Oral Steroids for Acute Cough) Trial is to determine whether oral prednisolone (40 mg daily for 5 days) can reduce the duration of moderately bad (or worse) cough and the severity of all its associated symptoms on days 2 to 4 post-randomisation (day 1 is trial entry) by at least 20% in adults ≥18 years with acute LRTI presenting to primary care.

**Methods/design:**

OSAC is a two-arm, multi-centre, placebo-controlled, randomised superiority trial. The target sample size is 436 patients, which allows for a 20% dropout rate. Patients will be recruited from primary care sites (General Practitioner surgeries) across England and followed up until symptom resolution. The two primary clinical outcomes are the duration of moderately bad (or worse) cough, and the severity of all its associated symptoms on days 2 to 4 post-randomisation. Secondary outcomes include: antibiotic consumption; symptom burden; adverse events; participant satisfaction with treatment and intention to consult for future similar illnesses. A parallel economic evaluation will investigate the cost-effectiveness of the intervention.

**Discussion:**

Results from the OSAC trial will increase knowledge regarding the clinical and cost-effectiveness of corticosteroids for LRTI, and will establish the potential of a new treatment option that could substantially improve patient health. We have chosen a relatively high ‘efficacy dose’ as this will enable us to decide on the potential for further research into lower dose oral and/or inhaled corticosteroids. This trial will also contribute to a growing body of research investigating the natural course of this very common illness, as well as the effects of steroids on the undesirable inflammatory symptoms associated with infection.

**Trial registration:**

Current Controlled Trials ISRCTN57309858 (31 January 2013).

**Electronic supplementary material:**

The online version of this article (doi:10.1186/s13063-015-0569-5) contains supplementary material, which is available to authorized users.

## Background

### Epidemiology, costs and current management of lower respiratory tract infection

Lower respiratory tract infection (LRTI), defined as an acute cough with at least one of sputum, chest pain, shortness of breath and/or wheeze [1], is one of the most common conditions managed in primary care in the UK and internationally [2]. Over 75% of patients presenting to primary care for this condition are prescribed antibiotics [3,4] and have a 20% likelihood of re-consulting within the same illness episode [1]. Acute cough is estimated to cost the UK National Health Service (NHS) at least £20 million annually in prescription costs and £170 million in consultation costs [5,6]. Patient costs have been shown to be in excess of £15 per episode [7], and respiratory tract infection is one of the most common reasons for work absenteeism [8].

Despite good evidence that antibiotics do not reduce the duration or severity of LRTI symptoms [2,5,9], they continue to be widely prescribed [2,5]. This is adding to the significant rise in antimicrobial resistance [10], which is an increasing and serious threat to public health [11,12]. Novel therapeutic measures are urgently needed [6], and so far evidence of efficacy for alternative treatments has not been demonstrated [13].

### Rationale for testing the effectiveness of corticosteroids in lower respiratory tract infection

Symptoms of LRTI include cough, wheeze and shortness of breath, which are similar to the symptoms of exacerbated asthma [14,15]. Evidence suggests that the worst symptoms may last up to 1 week, while complete symptom resolution may take 3 weeks or more [5]. Prolonged symptoms are thought to be due to a transient bronchial hyper-responsiveness [16,17] and experimental evidence suggests similar changes to bronchial epithelium in people with and without asthma during a respiratory tract infection. Both groups have been shown to have significant reductions in Forced Expiratory Volume (FEV), as well as airways inflammation [14].

Oral and inhaled corticosteroids are widely prescribed for the treatment of acute and chronic asthma, respectively, and work by exerting an array of anti-inflammatory effects [18]. There is increasing interest in the potential role of corticosteroids in modifying the undesirable effects of infection-associated inflammation [19]. Benefits have already been demonstrated for children with acute croup [20] and community-acquired pneumonia (if also given β agonists) [21], adults hospitalised with community-acquired pneumonia [22], adults with post-infectious persistent cough [23] and adults with acute tonsillitis [24].

At the time of writing there have been no published studies of oral corticosteroid therapy for acute cough following respiratory tract infection [6]; however, a number of trials of inhaled corticosteroids have been conducted, of which one [25] is relevant to the Oral Steroids for Acute Cough (OSAC) trial. This tested the effects of high-dose fluticasone, 1 mg twice daily, (equivalent to 2 mg twice daily of beclometasone [26] or 8.5 mg of oral prednisolone [27]) for 2 weeks in non-asthmatic adults presenting to Dutch primary care with a cough (LRTI) lasting more than 2 weeks. The inhaled corticosteroids were effective in reducing the mean cough frequency score among non-smokers, but the clinical importance of the reduced cough score is uncertain and there was no economic evaluation.

We are aware of two other ongoing trials currently registered on the International Controlled Trials Register [28] to investigate the value of corticosteroids for other infectious illnesses in primary care: the TOAST (Treatment Options without Antibiotics for Sore Throat) trial (ISRCTN17435450); and the OSTRICH (Oral STeroids for Resolution of otitis media with effusion In CHildren) trial (ISRCTN49798431).

Research and anecdotal evidence suggests that European clinicians have started prescribing corticosteroids for LRTI (in the absence of chronic obstructive pulmonary disease (COPD)) [29], even though there is limited evidence to support their use for this condition.

Long-term steroid use is known to be associated with an array of unwanted systemic side effects such as adrenal suppression, impaired skin collagen synthesis and metabolic disturbances [30,31]. However, in the absence of specific contraindications [30,32], a short (up to 1 week) course of high-dose corticosteroids is considered to be safe and associated with few side effects [32-34].

The rationale for testing the effectiveness of corticosteroids in LRTI can be summarised as follows: (i) there is good evidence of oral steroid effectiveness for acute asthma; (ii) the symptoms of LRTI overlap with those of acute asthma; (iii) prednisolone (tablets at a dose of 40 mg daily for 5 to 7 days) is the most commonly used oral steroid for acute asthma; (iv) there is pharmacokinetic evidence to suggest that a minimum dose of 20 mg daily is required for non-asthmatic patients [35]; and (v) it is important that the first trial of its kind uses an adequate dose to detect any potential effects as a proof of concept.

### Rationale for the trial design

This double-blind randomised controlled trial will provide high quality evidence to determine whether steroids are effective in the symptomatic treatment of acute LRTI, for which, to date, non-steroidal anti-inflammatory drugs [13], antibiotics [9] and inhaled corticosteroids [6] have been shown to be ineffective. A double-blinded, maximum dose design has been chosen since: (i) the primary outcomes are subjective (in that cough severity is reported by the participant); and (ii) treatment with this agent for this clinical problem is novel, making a trial demonstrating effectiveness under optimal conditions important.

‘Duration of moderately bad or worse cough’ and ‘mean severity of all LRTI symptoms on days 2 to 4 post-randomisation’ have been selected as the primary outcomes for this trial, in order to test the hypothesis that the anti-inflammatory effects of corticosteroids will relieve both the duration and severity of the unwanted bronchospasm and other inflammatory side-effects of infection. In another study, participants reported symptoms between days 2 and 4 as being the worst problem [2], which provides the rationale for the timing for the second primary outcome in this trial.

We recognise the undesirability of further medicalisation of common and self-limiting infections in primary care [36], and if this trial demonstrates a clinically important treatment effect, we do not think it will be appropriate to promote the routine use of high-dose corticosteroids for acute LRTI (though we recognise that the prescription of corticosteroids to alleviate the most acute symptoms of chest infections remains a clinical decision). Rather, we think the implication will be that further trials of lower-dose oral or inhaled corticosteroids should be conducted. If no treatment effect is found, it is unlikely that further, lower-dose steroid research would be warranted for acute LRTI.

### Research questions

#### Primary research question

Can the use of oral prednisolone reduce the duration of moderately bad or worse cough and/or the severity of all its associated symptoms on days 2 to 4 post-randomisation by at least 20% when compared to placebo treatment in adults 18 years and over presenting to primary care with acute LRTI?

#### Secondary research questions

We will also: 1) assess the effects on antibiotic consumption; 2) estimate the cost-effectiveness from the perspectives of the NHS, patients, and society; 3) compare the burden, severity and duration of abnormal peak flow and LRTI symptoms; 4) compare adverse events including any new symptoms or worsening of existing symptoms, re-consultations for a documented deterioration in illness and serious adverse events; 5) investigate if participants’ subjective or objective response to oral steroids is associated with a clinical diagnosis of asthma or COPD; and 6) assess participants’ satisfaction with treatment and intention to consult for future similar illnesses.

## Methods/design

This study is a placebo-controlled, individually randomised, superiority trial in UK general practice.

### Eligibility

We wish to test the effects of corticosteroids in adults presenting to primary care with acute LRTI, in whom there is no evidence of pneumonia or other reason to require an immediate antibiotic or hospitalisation, and in whom there is no reason to consider the use of oral prednisolone 40 mg daily for 5 days unsafe. At the same time, the relatively high dose used in this trial requires stringent exclusion criteria to ensure patient safety. The eligibility criteria are as follows:

#### Inclusion criteria

The following inclusion criteria must all apply:Aged 18 years or over;Consulting for an acute (≤28 days) cough as the main presenting symptom;In the past 24 hours, the patient has had at least one of the screening symptoms listed below (a-d), localising to the lower respiratory tract and suggestive of an acute LRTI:phlegm (sputum)chest painshortness of breathwheezePatient and practice have sufficient time for consent and randomisation into the trial by the end of the day of consultation, or the next working day as long as this is within 24 hours;Patient able and willing to give informed consent themselves;Patient able and willing to complete the daily symptom diary themselves;Patient able, willing and available to receive weekly telephone calls from the trial team.

#### Exclusion criteria

The presence of any of the following exclusion criteria warrants exclusion:Known lung cancer or chronic lung disease (for example, cystic fibrosis, COPD, bronchiectasis);Has an ‘active’ diagnosis of asthma (for which any treatment has been given in the past 5 years);The patient’s LRTI warrants same day hospital admission or immediate antibiotics (note: use of delayed prescription (post-dated by at least one working day after the randomisation date) does not preclude OSAC trial participation):According to NICE guidelines, the patient warrants immediate antibiotic treatment by virtue of one or more of the following:A.Is clinically very unwell or has symptoms and signs suggestive of pneumonia, for example tachypnoea (>20 bpm), unilateral chest signs or consolidation, or hypoxia (oxygen saturation <94%) or other systemic infection, for example suspected bacteraemiaorB.Is at high risk of complications, including patients with chronic heart, chronic lung (for example, COPD, bronchiectasis and cystic fibrosis), chronic renal, chronic liver or neuromuscular disease or immunosuppression; or with complications from previous episodes of lower respiratory tract infection, for example hospital admission for pneumoniaorC.Aged over 65 years with at least two of the following criteria, or aged over 80 years with at least one of the following criteria:I.Unplanned hospitalisation within the previous yearII.Type 1 or Type 2 diabetesIII.History of cardiac failureRequires an oral or systemic antibiotic on the day of consultation to treat another infection unrelated to their acute cough, for example a co-existing cellulitis (note: use of topical antibiotics does not preclude OSAC trial participation);Recently (≤1 month) used inhaled corticosteroids;Recently (≤1 month) used short- (up to 2 weeks) course systemic corticosteroids;Currently using, or has previously (≤12 months) used systemic steroids for a cumulative period greater than 2 weeks, that is “long-term” use;Known to be pregnant, is trying to conceive or is at risk of pregnancy (for example, unwilling to take a reliable form of contraception) in the next month;Currently breast-feeding;This is not the patient’s usual practice, that is the patient is visiting or is not intending to stay with the practice for the 3 month trial follow-up period;Previously randomised into the OSAC trial;Has been involved in another medicinal trial within the last 90 days or any other clinical research study within the last 30 days;Is unable to give informed consent or complete the trial paperwork (including the symptom diary) through mental incapacity, for example major current psychiatric illness, learning difficulties and dementia;Known immune-deficiency, for example chemotherapy causing immunosuppression, asplenia or splenic dysfunction, advanced cancer or HIV infection;Patient due to receive the shingles vaccine in conjunction with the influenza vaccine;Has any of the following (A-P) known contraindications or cautions to oral steroids:Current or previous history of:A.Peptic ulcer diseaseB.Previous tuberculosis (TB)C.No previous chickenpox and known recent (≤28 days) history of close personal contact with chickenpox or herpes zosterD.Known allergy to prednisolone or other OSAC trial tablet ingredients (potato starch, lactose monohydrate, colloidal silicon dioxide, sodium starch glycolate, magnesium stearate), galactose intolerance, Lapp lactase deficiency or glucose-galactose malabsorptionE.OsteoporosisF.GlaucomaG.Suspected ocular herpes simplexH.Cushing’s diseaseI.EpilepsyJ.Severe affective disorders, for example manic depression, previous steroid psychosisK.Previous steroid myopathyL.Intention to use a live vaccine in the next 8 weeks or has received a live vaccine in the previous 2 weeks (note: assess live vaccine status by cross-checking with the British National Formulary)Current history only:M.Uncontrolled diabetes (glycated haemoglobin or HbA1C >8%)N.Uncontrolled hypertension (note: as per Responsible Clinician’s routine clinical judgement)O.Taking other interacting medication (e.g. phenytoin and anti-coagulants)P.Any other British National Formulary listed contraindication or caution (note: as per Responsible Clinician’s routine clinical judgement)Is unable to swallow tablets

To meet the recruitment target and to ensure a generalisable patient population, recruitment will take place across four collaborating UK trial centres: the Universities of Bristol, Nottingham, Oxford and Southampton.

### Intervention and blinding

Participants will be randomly assigned to one of two treatments: (i) 2 × 20 mg oral prednisolone tablets daily for 5 days or (ii) 2 × 20 mg oral placebo tablets daily for 5 days. Participants may stop taking the trial medication before the 5 days if they feel completely better for two consecutive days. Participants, clinicians and the trial team (including the statisticians) will all be blinded to allocation. All participants randomised to the trial will continue to receive usual clinical care.

### Treatment allocation, concealment and emergency unblinding

The computer-generated randomisation schedule will be produced by a statistician who is independent of the OSAC trial statisticians, and stratified by centre using a variable block size. The schedule will be held by the Pharmacy of the University Hospitals Bristol NHS Foundation Trust (“the Pharmacy”), who will allocate medicine packs containing active and placebo tablets and identified by a unique Medicine ID number, to identical, sequentially numbered Patient Packs identified by a unique Participant ID number, which will then be sealed. Packs, which are indistinguishable between active and placebo groups, are issued sequentially to eligible, consented patients at recruiting primary care sites. Clinicians, patients and all members of the research team were masked to the randomisation sequence, and all outcome data were gathered masked to allocation status.

The use of distinct Participant ID and Medicine ID numbers will enable flexibility in the number of patients recruited at each of the four trial centres. Medicine packs can be combined with patient packs as needed, allowing for temporary differential fluctuations in recruitment rates between centres. The four centres will be provided with Patient Packs to distribute to the participating primary care sites in blocks of four (although larger numbers of packs will be issued to practices with proven capacity to recruit to this trial).

The Pharmacy will hold the master drug allocation log and provide a 24 hour emergency unblinding service based on a standard operating procedure for breaking the code in the event of a medical emergency. Trial participants will be given a Trial Participation Card with details of who their Responsible Clinician should contact in the event of an emergency, and all practice-based clinicians will receive training in the use of the emergency unblinding service.

At the end of the trial, the code-break will only be released to the investigative team once written confirmation has been received that primary outcome data analysis is complete.

### Outcomes

#### How the outcome measures will be ascertained

The OSAC trial will use validated patient completed symptom diary methods [37] that have been used in a number of similar previous trials [2,5]. Participants will record in the diary the severity of the following symptoms: cough; phlegm; shortness of breath; sleep disturbance; feeling generally unwell; activity disturbance. A symptom score scale of 0 to 6 will be used (0 = no problem, 1 = very little problem, 2 = slight problem, 3 = moderately bad, 4 = bad, 5 = very bad, and 6 = as bad as it could be) which is shown to be sensitive to change and internally reliable [5]. For this trial, we will record all the above symptoms for up to 28 days (or until symptom resolution for two consecutive days) since LRTI duration has been previously shown to last 3 to 4 weeks [5]. Cough duration and severity will be measured for up to 8 weeks since effects on these may not be apparent for some time after using corticosteroids.

For this trial, participants will also record their peak expiratory flow in the morning and the evening for the duration of their illness up to 28 days, and measure their quality of life at weekly intervals (up to 4 weeks) using the EQ-5D-5L validated questionnaire [38], which has been shown to be moderately responsive in participants with acute cough/LRTI, and is a suitable measure for use in economic evaluation studies of this illness [39].

#### Primary outcome measures

Duration of moderately bad or worse cough (using a validated web/paper-based symptom diary containing an item asking participants to rate their cough from 0 to 6 (as described in ‘How the outcome measures will be ascertained’ above). Duration is calculated as the number of days from randomisation to the last day that the participant scored 3 or higher, where that last day is followed by at least two consecutive days where the score is less than 3;Mean of all symptom severity scores on days 2 to 4 post randomisation, measured using the symptom diary. Severity of symptoms is scored 0 to 6 as for cough, detailed above. Symptoms include cough, phlegm, shortness of breath, disturbed sleep, feeling generally unwell, and interference with normal activities/work. A mean score will be calculated across these symptoms for each of days 2, 3 and 4 and then an overall mean calculated.

#### Secondary outcome measures

Antibiotic consumption;Duration of corticosteroid tablet use;Total duration and severity of symptoms (cough; phlegm; shortness of breath; wheeze; blocked/runny nose; chest pain; fever; muscle aching; headache; sleep disturbance; feeling generally unwell; activity disturbance), until the severity of each is scored by the participant as ‘1’ or ‘very little problem, and abnormal peak flow (defined as a peak flow reading that is not within the range of values that would be expected according to a standard predictive algorithm based on gender, height and weight);Adverse events including re-consultation for a documented illness deterioration;Patient satisfaction with treatment and intention to use the same treatment if it were to be available in the future;Clinical diagnosis of asthma, COPD, whooping cough (pertussis), or lung cancer at 3 months;Quality of life (using the EQ-5D-5L);NHS treatment and investigation costs, out-of-pocket patient and family costs, and the cost to society of time off work.

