#### Analysis of secondary outcomes

The secondary outcomes listed above (see “Secondary outcome measures”) will be analysed using appropriate regression models and will adjust for the baseline measure of the outcome, where possible, and centre.

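### The only peak flow outcome is readings outside a predicted range, so change within the range is not counted; add measured, baseline-adjusted peak flow as a continuous outcome

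*Protocol article*

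**What the plan says.** All references are to the protocol article.

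- **Data collected** (How the outcome measures will be ascertained): "participants will also record their peak expiratory flow in the morning and the evening for the duration of their illness up to 28 days".
- **Outcome** (Secondary outcome measures): duration and severity of symptoms and "abnormal peak flow (defined as a peak flow reading that is not within the range of values that would be expected", the range coming from a formula using gender, height and weight.
- **Question** (Secondary research questions): "compare the burden, severity and duration of abnormal peak flow and LRTI symptoms".
- **Analysis** (Analysis of secondary outcomes): the listed outcomes "will be analysed using appropriate regression models and will adjust for the baseline measure of the outcome, where possible, and centre". No further peak flow variable is introduced there.
- **Population** (Exclusion criteria): "Known lung cancer or chronic lung disease" is excluded, as is asthma "for which any treatment has been given in the past 5 years".
- **Mechanism** (Rationale for testing the effectiveness of corticosteroids): of people with and without asthma during a respiratory infection, "Both groups have been shown to have significant reductions in Forced Expiratory Volume (FEV), as well as airways inflammation".

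**The concern.** A numeric series is collected, and the outcome definition then cuts each reading at the limits of a predicted range. The cut is part of the outcome itself and appears both there and in the research question, so it is not a modelling detail left for later. An analysis plan that follows the article inherits it.

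Two features make the cut unattractive here. The exclusions mean that many participants may be within the range, although the article gives no proportion and undiagnosed disease is possible (asthma and COPD diagnoses at 3 months are themselves recorded). The rationale also expects a temporary fall in lung function in people without asthma. A fall and recovery that stay inside the range would fit that mechanism and would score nothing.

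Peak flow is the only physiological measure among the listed outcomes, and the article describes both primary outcomes as subjective. At stake is the information drawn from readings already collected.

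**Working it through.** **The plan's own figure.** The article gives no peak flow SD, effect, share abnormal or power. Its only usable input is the number analysed per arm. From Sample size calculation: log-scale difference 1.555 − 1.333 = 0.222, SD 0.637, two-sided alpha 0.05, power 90%. Then n = 2 × (1.960 + 1.282)² × 0.637² / 0.222² = 173.0, rounded up to 174 per arm; 174 / 0.8 = 217.5, so 218 per arm and 436 in total. This agrees with the article, and 174 per arm is used below.

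**Assumptions (none from the article).** Peak flow in % predicted; between-patient SD 12 or 18; within-patient SD 6 per day; lower limit 80%; average flow 80, 90 or 100; only low readings counted as abnormal; a uniform gain of 4 points on active treatment.

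**Power for the unadjusted mean.** SD of a patient's mean = √(between² + 6²/days); z = 4 / (SD × √(2/174)); power = Φ(z − 1.96).

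- SD 12, 3 days: √(144 + 12) = 12.49; z = 4/1.339 = 2.99; power 85%.
- SD 18, 3 days: √(324 + 12) = 18.33; z = 4/1.965 = 2.04; power 53%.
- SD 12, 28 days: √(144 + 1.29) = 12.05; z = 4/1.292 = 3.10; power 87%.
- SD 18, 28 days: √(324 + 1.29) = 18.04; z = 4/1.934 = 2.07; power 54%.

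**Power for number of abnormal days** (Mann-Whitney test, 1,000 simulated trials per setting):

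| SD | Average flow | Days 2–4: mean | Days 2–4: abnormal days | 28 days: mean | 28 days: abnormal days |
|---|---|---|---|---|---|
| 12 | 80 | 85% | 74% | 87% | 82% |
| 12 | 90 | 85% | 64% | 87% | 78% |
| 12 | 100 | 85% | 41% | 87% | 61% |
| 18 | 80 | 53% | 42% | 54% | 49% |
| 18 | 90 | 53% | 37% | 54% | 45% |
| 18 | 100 | 53% | 28% | 54% | 34% |

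The gaps in the table are 11 to 44 points over days 2 to 4 and 5 to 26 points over 28 days. Simulated values move by a few points between runs, so the honest statement is roughly 10 to 50 and roughly 4 to 29. The gap widens as more participants are in range: at SD 12 the share of control readings below 80 is Φ((80 − average)/√(144 + 36)), which is 50%, 23% and 7% at averages of 80, 90 and 100.

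**Does scoring severity recover the loss?** Using the mean shortfall below 80 over days 2 to 4, power is 78%, 62% and 38% at SD 12, and 46%, 37% and 27% at SD 18. It helps a little when half the readings are low and hardly at all otherwise.

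**Gain confined to participants with true flow below 80** (average 90, SD 12, gain 12 points):

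| Window | Unadjusted mean | Abnormal days | Mean adjusted for one pre-treatment reading |
|---|---|---|---|
| Days 2–4 | 51–53% | 79–80% | 94% |
| 28 days | 56% | 51–54% | 98% |

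With an 8-point gain over days 2 to 4, the unadjusted mean has 26% and abnormal days 40%. The adjusted figures assume a stable patient level and an early reading with error SD 6, that is, a correlation between single readings of 144/180 = 0.80. A noisier early reading, or recovery at different speeds, would shrink that advantage.

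**Literal two-sided range.** With limits at ±1.645 SD and controls centred on predicted, 10.0% of readings are outside. After a 0.3 SD improvement the share is Φ(−1.945) + 1 − Φ(1.345) = 2.6% + 8.9% = 11.5%. An improvement then raises the abnormal share.

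**The case against.** The strongest objection is that the loss depends on the pattern of effect. The article's reasoning includes relief of bronchospasm, so benefit confined to people with reduced flow is at least as plausible as a uniform gain. In that case abnormal days beat an unadjusted mean over days 2 to 4 and nearly match it over 28 days. This stands, and it rules out a plain unadjusted mean as the remedy. Adjustment for an early reading restores the advantage of the continuous measure, although the comparison is not fully like for like because the abnormal-days test was unadjusted.

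Next, days 2 to 4 is the window of the symptom severity primary outcome, not of peak flow, which is recorded for up to 28 days. This also stands: the smaller 28-day losses are closer to what the article sets out.

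Third, how burden and severity are scored is commonly left to the full protocol or analysis plan, neither of which is shown. That is fair for scoring, but the restriction to abnormal readings is stated in the article itself.

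A reader might go further and infer that a null peak flow result is likely even if steroids improve airflow, and that it would be read as evidence against the mechanism. Neither is supported. At SD 12 over 28 days the abnormal-days analysis keeps 61% to 82% power under a uniform gain, and at SD 18 even the unadjusted mean has only about 54%. The article ties its conclusions to whether a treatment effect is found and sets no peak flow criterion. Nor is the outcome blind to the drug in everyone who starts in range, since deterioration out of the range is counted.

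**Conclusion.** The point holds as a low-cost improvement. The article fixes its only peak flow outcome as readings outside a predicted range, which discards change within the range and, taken literally, treats high readings as abnormal. The size cannot be read from the article. Under a uniform 4-point gain with the inputs assumed above, the cut costs roughly 10 to 50 points of power over days 2 to 4 and roughly 4 to 29 over 28 days against an unadjusted mean, the larger losses arising when most participants are in range. It is not established that the cut loses power under every pattern of effect: with benefit only in those with low flow, the continuous analysis needs baseline adjustment to come out ahead. Peak flow is one of many secondary outcomes and carries no power claim, so nothing here touches the primary outcomes or the 436 sample size.

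**What to change.** In Secondary outcome measures, add measured peak expiratory flow (litres/min or % predicted) as a continuous outcome over the recorded period. Analyse it by regression or a repeated-measures model adjusted for centre and for baseline, as Analysis of secondary outcomes already provides. Use the trial-entry or day 1 reading as baseline where available, and otherwise adjust for sex, age and height. Keep duration of abnormal peak flow as a reported secondary outcome, and state that only readings below the range count as abnormal.

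The cost is outcome and analysis wording, one more secondary analysis, and a mean difference that is less directly interpretable than days abnormal. No new data are needed. Recruitment has ended, so the change should be dated and documented before the code-break is released.
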